### Randomization and masking

After an initial assessment examination confirming eligibility and collection of baseline data, participants will be allocated by a physician using computer-generated block randomization in a ratio of 1:1 to the experimental group or control group. The allocations will be concealed in sequentially numbered, opaque, sealed envelopes with a signature across the sealing point.

Because of the nature of the intervention, physical therapists and patients cannot be blinded when offering or receiving the treatment. However, patients will be asked not to reveal their group allocation to ensure blinding of the evaluator. To minimize bias, strict eligibility will be maintained in the whole trial, and there are separate rooms for assessment and treatment, so that each group will hardly know much about each other. A trained evaluator blinded to group allocation will complete all patient assessments at baseline and immediately after the 6-month intervention. Both groups will continue with their routine activities, but they will not be able to attend any other formal exercise program. The statistician will not be aware of the data coding. Figure 2 illustrates the timing of all trial processes (Additional file 2).

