### Control group program

Control subjects will receive the standard of care according to the SRS criteria: observation for patients with curves between 10 degrees and 25 degrees [9] and attendance at the study assessments. The control group will only attend study assessments and not the therapy sessions.

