### Suspension criteria

In the interim analysis, clinical significance is defined as a 5-degree Cobb angle change, which is the reliability of radiographic examination and the international “gold standard” for minimally significant clinical change [31]. Decreasing or remaining in Cobb angle of 5 degrees means the treatment is successful, whereas increasing the Cobb angle to greater than 5 degrees is defined as failure of treatment [32]. There are no standard stopping criteria for specific exercise therapy outcome. Previous studies showed that there is a 40% failure rate for standard care (observation) [18]. In light of the clinical practice as well as the previous studies, the stopping criteria used in this protocol are as follows:If more than 40% of patients fail in either the experimental group with three-dimensionally integrated exercise for scoliosis or the control group, the trial will be ended, suggesting a change of treatment.During the whole study period, if the patient has significantly abnormal progression in clinical examination and the Cobb angle has reached ≥ 25 degrees, the patient (in either the experimental group or the control group) will be suspended from the study.

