### Assessment

The following demographic data and patient characteristics of the experimental group will be collected: age, gender, height, weight, body mass index, Risser sign, time since menarche for female patients, curve pattern, apex levels, and exercise compliance. Skeletal immaturity based on the Risser stages will be recorded for each patient at the first assessment. Curvatures will be classified according to the Ponseti classification system, which distinguishes four major types of scoliosis: thoracic, lumbar, thoracolumbar, and S-shaped [8, 33]. Development of the ossification of the iliac crest is used to assess the remaining spinal growth, and the stage of ossification of the iliac apophysis can be seen on a radiograph. The Risser sign is an assessment of skeletal maturity and spinal growth. It is based on the ossification of the iliac apophysis, which is evaluated with a four-grade scale from 0 (no ossification) to 5 (fused ossified apophysis) [34]. The outcome measures described in the subsections that follow will be performed before and after 6 months of intervention in both groups.

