### Data collection, data management, and statistical analysis plan

The primary outcome is the change of Cobb angle, and the secondary outcome measures will include the ATR, sagittal index, and quality of life. Descriptive statistics will be calculated for baseline demographics, physical examination, radiographs, and questionnaire data, and results will be presented as the mean ± SD, whereas categorical variables will be expressed as percentages. The chi-squared test will be used to compare the categorical/dichotomous variables. Separate analyses will be conducted for each outcome.

Data will be entered using EpiData software designed for this study. All data will be collected, typed, and analyzed by a masked statistician who will not have access to study assignment. The main investigators will check the data every 2 weeks to ensure the quality.

The primary endpoint is the pre- and posttreatment difference in the Cobb angle. We have calculated that a sample size of 21 patients per group would be capable of detecting a between-group difference of 5 degrees in the primary endpoint with a type I error of 5% and a power of 95% [20]. Because the interval of Cobb angles at entry is 10–20 degrees, and assuming a uniform distribution of Cobb angles in this range (the most unfavorable scenario), an SD of 5 degrees is estimated [8].

Baseline comparability will be assessed using Student’s *t* test for independent samples. To screen for variables associated with each of the outcome variables, univariate linear mixed models for each relevant covariable (age, gender, body mass index, Risser sign, time since menarche, apex levels, curve pattern, and compliance may have associations with risk of progression) will be conducted.

Multiple linear mixed models for each time point will be tested, including covariables found significant at *p* ≤ 0.20 in the univariate analysis, and after screening for multicollinearity [42].

For the ordinal outcome (SRS-22, which is based on only one item with five levels), generalized linear mixed effects model analysis will be used.

Furthermore, because subjects with younger than 13 years of age are characterized by a higher risk of progression [43], the patients will be divided into two subgroups (age < 13 years and age ≥ 13 years), and a linear mixed model analysis for the primary outcome will be performed on each subgroup.

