To assess differences in group changes from baseline to 6 months while adjusting for covariables, weighted estimating equations and a sensitivity analysis will be conducted as the primary approach to deal with the missing data, especially for the primary outcome of Cobb angle [44]. All the analysis will be carried out using IBM SPSS Statistics for version 20.0 software (IBM, Armonk, NY, USA).

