## Discussion

This study protocol describes an RCT that is designed to evaluate the efficacy of three-dimensionally integrated exercise on scoliosis measured as Cobb angle, the ATR in degrees, sagittal profile, and quality of life in patients with mild AIS.

In this study, the patients and intervention team are not blinded, because the intervention team needs to carry out the detailed treatment plan with the patients, and the patients in each group know their treatment plan. The assessor, enrollment assistant, and statisticians are blinded with respect to the patients’ treatment allocation. Meanwhile, there are separate rooms for assessment and treatment to avoid having other patients know about the treatment. The control group only needs to perform the assessment at the baseline and after the 6-month intervention, so they will have less time to communicate with the other patients. Once the patient asks to change the treatment plan, they will be eliminated from the study immediately.

Preventing the curve progression is the most important reason for treatment. There is still no intervention to cure AIS [1, 8]. The results of this RCT will provide valuable information for the family, patient, clinicians, and clinical decision makers, as well as to administrative stakeholders, and they may play an important role in providing healthcare services.

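### Patients are removed from the study, not only from assigned treatment, when the curve reaches 25 degrees or they ask to change treatment, so missing 6-month Cobb values depend on the primary outcome

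*Protocol article*

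**What the plan says.** Two rules in the Protocol article end study participation.

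- *Suspension criteria*: "if the patient has significantly abnormal progression in clinical examination and the Cobb angle has reached ≥ 25 degrees", then "the patient (in either the experimental group or the control group) will be suspended from the study". Both conditions must hold, and the rule covers both arms.
- *Discussion*: "Once the patient asks to change the treatment plan, they will be eliminated from the study immediately".

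The endpoint and its timing are fixed elsewhere. The analysis section states: "The primary endpoint is the pre- and posttreatment difference in the Cobb angle". *Randomization and masking* places assessments "at baseline and immediately after the 6-month intervention", and *Assessment* says that the outcome measures "will be performed before and after 6 months of intervention in both groups". No measurement is scheduled in between.

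Contact differs by arm. Exercise patients attend one or two supervised hospital sessions a week (*Experimental intervention program*). For controls: "The control group will only attend study assessments and not the therapy sessions".

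On missing data, the analysis section states that "weighted estimating equations and a sensitivity analysis will be conducted as the primary approach to deal with the missing data", with particular mention of the Cobb angle.

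**The concern.** The first rule is triggered by the variable that the trial is designed to compare. The second is triggered by wanting different care, which may well be related to how the curve is behaving. In both cases the patient leaves the study, so on the stated schedule no 6-month Cobb angle would be obtained.

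Entry requires a Cobb angle of 10 to 20 degrees. A patient who reaches 25 has therefore worsened by at least 5 degrees, so the first rule can remove only large worsenings. Weighted estimating equations correct for dropout when the chance of being observed is explained by recorded data. Here that chance depends on the outcome. There is no scheduled intermediate measurement, no stated use of the triggering value, and only a handful of dropouts from which to estimate weights.

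At stake are the as-randomised comparison of Cobb change and the count of failures used in the 40% stopping criterion.

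**Working it through.** **The plan's own figure.** *Sample measurement* gives changes of −1.55 (SD 4.39) for exercise and 2.90 (SD 2.60) for control. The difference is 4.45, the pooled SD is √((4.39² + 2.60²)/2) = 3.61, and d = 4.45/3.61 = 1.23. A two-sided t test at 0.05 has power 0.949 with 18 per arm and 0.959 with 19, so the stated 19 is reproduced. The plan recruits 21 per arm for 10% attrition, which is 0.10 × 21 = 2.1 patients.

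**Model for the 25-degree rule.** Entry angle b is uniform on 10 to 20 (the analysis section's own assumption). Change is normal with mean m and SD s, independent of b (assumption). Everyone with b + change ≥ 25 is removed. With u = (25 − b − m)/s:

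- proportion removed: p = (1/10) ∫ [1 − Φ(u)] db
- removed patients' contribution to the mean: e = (1/10) ∫ {m[1 − Φ(u)] + s·φ(u)} db, so their mean change is e/p
- mean among those retained: (m − e)/(1 − p)

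**Planning inputs.**

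- Exercise: p = 1.3%, mean change of those removed +8.42. Retained mean = (−1.55 − 0.0131 × 8.42)/0.9869 = −1.68.
- Control: p = 3.1%, mean change of those removed +7.50. Retained mean = (2.90 − 0.0308 × 7.50)/0.9692 = 2.75.
- Difference: −4.45 for all randomised, −4.44 for those retained. The shift is about 0.01 degree.

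**Control failure at 40%.** *Suspension criteria* quotes this rate for observation, with failure meaning an increase of more than 5 degrees. The control mean must then be m = 5 − 0.253 × s. The control SD is an assumption; the exercise arm is as above.

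| Control SD | Control mean | Controls removed | Of 21 | Retained control mean | Difference, all → retained | Shift |
|---|---|---|---|---|---|---|
| 2.60 | 4.34 | 7.4% | 1.6 | 4.05 | −5.89 → −5.73 | 0.16 |
| 4.39 | 3.89 | 12.4% | 2.6 | 3.02 | −5.44 → −4.70 | 0.74 |

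In these scenarios the shift is towards no difference. In the second row this rule alone exceeds the attrition allowance of 2.1 patients.

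**The direction can reverse.** Give both arms a true mean change of 2.90 and keep the planning SDs of 4.39 and 2.60. The rule then removes 8.9% of exercisers and 3.1% of controls. Retained means are 2.24 and 2.75, so a true difference of zero appears as about −0.5 degree in favour of exercise.

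**Failure count.** If removed patients were left out of the count, a true control failure rate of 40% would appear as (0.400 − 0.074)/0.926 = 35% in the first row and (0.400 − 0.124)/0.876 = 31.5% in the second. The protocol does not say whether they are counted.

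**Limits of the model.** It removes everyone who ends at 25 or more. It ignores the separate requirement of clinical progression, and it ignores curves first found at the 6-month visit, whose endpoint value would already exist. The shifts are therefore upper illustrations within each scenario. They also depend on the assumed spread: at a control SD of 5, again with 40% failure, the difference goes from −5.28 to −4.29.

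**The case against.** The strongest reply has four parts.

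- **An article condenses the protocol.** Handling of patients who stop may be set out elsewhere, and the analysis section does plan weighting and a sensitivity analysis. This stands as to detail. But study exit is something the article states, not something it omits, and no analysis method replaces a measurement that the stated rules do not provide for.
- **The triggering radiograph may be kept.** A reader might infer that the value is discarded. The document does not say so; it is silent. If the value were kept and used, part of the problem would go away, which is why the fix asks for it to be stated.
- **The losses need not fall mainly on the controls.** A reader might infer that they would, because observed patients are expected to progress more. The visit schedule does not support this. A control whose curve passes 25 degrees would usually be found at the 6-month visit, with the endpoint in hand, whereas an exerciser seen weekly may be detected and suspended earlier. The direction is unknown.
- **The effect is tiny under the plan's own inputs.** This is correct for the 25-degree rule. The larger figures rest on a failure rate from a cited study, whose follow-up length the article does not give, and on assumed control SDs.

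Two further inferences also go too far. Any figure for controls leaving to seek other treatment, such as 10 to 20% of them, has no source in the document. Nor is there a rule removing poorly adherent exercisers: compliance below 70% leads to joint problem-solving under *Compliance supervision*.

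**Conclusion.** The point holds as a defect in the stated rules: patients leave the study because of the primary outcome or because they want other treatment, with no stated provision for measuring them afterwards or using the triggering value. The planned weighting cannot be relied on to correct this.

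The size of the bias is not established. For the 25-degree rule it is about 0.01 degree under the planning inputs and at most about 0.2 to 0.7 degrees if controls fail at about 40%, given a control change SD of 2.6 to 4.4, uniform entry at 10 to 20 degrees, and change independent of entry angle. The treatment-change rule may matter more or less than this; the document gives no basis for a figure. It would be too strong to say that the randomised comparison is destroyed. The case for acting is that unmeasured outcomes cannot be recovered later and the remedy is cheap.

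**What to change.** Leave the clinical decisions, including the 25-degree threshold, as they are. Change the wording in *Suspension criteria* and *Discussion* so that stopping or changing assigned treatment is distinct from leaving the study. Then state that:

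1. the planned 6-month assessment is obtained for every randomised patient unless consent is withdrawn;
2. patients are analysed in the arm to which they were randomised;
3. the Cobb value that triggered the rule is kept as observed data and used when the 6-month value is unavailable;
4. failure is classified by the protocol's own definition, an increase of more than 5 degrees. Reaching 25 should not count as failure automatically: a curve going from exactly 20 to exactly 25 has risen by 5 degrees, not by more than 5.

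The cost is a wording amendment and attendance at a visit already planned. The downside is that outcomes measured after a change of treatment may dilute the contrast between arms.

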### Assessment

The following demographic data and patient characteristics of the experimental group will be collected: age, gender, height, weight, body mass index, Risser sign, time since menarche for female patients, curve pattern, apex levels, and exercise compliance. Skeletal immaturity based on the Risser stages will be recorded for each patient at the first assessment. Curvatures will be classified according to the Ponseti classification system, which distinguishes four major types of scoliosis: thoracic, lumbar, thoracolumbar, and S-shaped [8, 33]. Development of the ossification of the iliac crest is used to assess the remaining spinal growth, and the stage of ossification of the iliac apophysis can be seen on a radiograph. The Risser sign is an assessment of skeletal maturity and spinal growth. It is based on the ossification of the iliac apophysis, which is evaluated with a four-grade scale from 0 (no ossification) to 5 (fused ossified apophysis) [34]. The outcome measures described in the subsections that follow will be performed before and after 6 months of intervention in both groups.

### Primary outcome measurement

#### Change of Cobb angle

It is recommended that curve magnitude be measured using the Cobb method on a standing frontal radiograph [20]. The Cobb angle of a scoliotic curve is defined as the angle formed by the intersection of two lines, one parallel to the endplate of the superior end vertebra and the other parallel to the endplate of the inferior end vertebra (Fig. 4). If the patient has double curves, the major curve will be calculated for analysis.

**Fig. 4 Fig4:**
[figure not shown]
The Cobb method of measurement

### Secondary outcome measurements

#### Angle of trunk rotation

The ATR will be measured with a Scoliometer™ [21, 22]. The Scoliometer™ measures the hump (ATR) appearing as a consequence of the Adam’s test. It is an evaluation tool that has proven highly useful [1, 8]. The patients will be asked to bend their trunk forward until it is parallel to the ground, keeping the palms of their hands together with their arms hanging down and perpendicular to their trunk. In this position (Fig. 5), the ATR values are obtained by positioning the center of the Scoliometer™ over the spinous process and perpendicular to the spine [35].

**Fig. 5 Fig5:**
[figure not shown]
Angle of trunk rotation

#### Sagittal index

The sagittal profile of the spine is frequently modified in patients with scoliosis and is extremely relevant in the management of this disease; thus, a sagittal measurement is recommended to evaluate kyphosis and lordosis [36]. The plumb line is an easy, quick, and reliable tool to assess the sagittal profile in clinical evaluation and clinical follow-up, as well as for the evaluation of the effectiveness of physiotherapy-specific exercises [23]. Measurement of the plumb line distance is measured from the apical spinous process of the occiput, the most prominent lordosis point on the neck, from C7, T5-T6, T12, L3, and S1 to the plumb line (Fig. 6). The sagittal index consists of the sum of the plumb line distances from C7 and L3; a value < 60 mm is considered to be a flat back; 60–90 mm is in the normal range, whereas a value > 90 mm is considered to indicate kyphosis [37, 38].

**Fig. 6 Fig6:**
[figure not shown]
Measurement of sagittal distance

#### SRS-22 dimension scores

The 22-item Scoliosis Research Society Outcomes Questionnaire (SRS-22) is especially designed for patients with idiopathic scoliosis [24]. The questionnaire consists of 22 items with 5 dimensions: function/activity, pain, self-image, mental health, and satisfaction with treatment. Each domain has five items each, except the satisfaction with treatment domain, which has only two items. The two satisfaction items are not included in the final analysis. Each item is scored from 1 (worst) to 5 (best). Results are presented as the mean of each scale (sum of 5 questions/5) and the mean subtotal score (sum of 20 questions/20) [39, 40]. In this study, we will use the validated Chinese version of SRS-22 [41].

### Adverse events

The physical therapist will record any adverse event occurring in this study.

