### Intervention

#### Experimental intervention program

The experimental group will receive a modified physiotherapeutic scoliosis-specific exercise intervention: the three-dimensionally integrated exercise for scoliosis program, which includes autocorrection in three dimensions, postural correction, breathing training, resistance training, muscle fascia releasing, functional activities, balance training, core stability training, proprioceptive input exercises, and patient education. Autocorrection exercise in three dimensions will be combined with specific breathing mode, and isometric contraction training to correct abnormal spinal physiological curvatures in the sagittal plane, accompanied by a wedge pad to modify humpback, waist asymmetry, and pelvic rotation in the horizontal plane. In breathing pattern training, the physical therapist will stimulate the concave areas of the thorax for patients during deep inspiration and will transfer stimulation to the convex side during deep expiration. While the patient is in coronal plane with longitudinal axial stretching, pelvic adjustments will be made to reduce the lateral curvature. During this period, the physical therapist will teach the patient how to combine these exercises with activities of daily living. All the patients in the experimental arm will receive treatment of one or two sessions weekly in the hospital under the supervision of a physiotherapist and one session per day at home under parental supervision. Some examples are shown in Fig. 3.

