### Interim analysis

An interim analysis will be performed on the primary endpoint of Cobb angle when enrolling 20 patients, including control group and experimental group, by a single statistician who is blinded to allocation and reports the results to the main investigators. The main investigators will discuss the results of the interim analysis with the monitoring board. In this study, the change of Cobb angle is the only primary outcome measurement; the secondary outcome measurements are the supporting elements for the whole outcome.

Our primary hypothesis is that the experimental intervention of three-dimensionally integrated exercise for scoliosis will optimize improvement in outcome effects (reduction in Cobb angle and improvement in multifidus activation). Effect sizes will be estimated using Cohen’s *d*, which corresponds to the mean difference between the groups in the change observed from baseline to 6 months (three-dimensionally integrated exercise for scoliosis standard of care), divided by the pooled SD at baseline (Cohen’s *d* ≥ 0.8 = large, 0.5–0.8 = moderate, 0.2–0.5 = small [45]). According to the previous study, the perceived mean global rating of change in the specific exercise group was 3.8 ± 2.2, corresponding to moderate improvement, and 0.3 ± 1.7 in the standard care group, corresponding to a small amount of deterioration [46]. In this study, an effect size change of 0.3 would be considered a significant finding to stop the study when performing the interim analysis [47]. The reasons for withdrawal from trial by arm will be calculated by the physical therapist.

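### The one adverse event recorder named is the unblinded physical therapist, who has scheduled contact with the exercise arm alone, so any event counts shown by arm are open to unequal ascertainment

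*Protocol article*

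**What the plan says.** Under Adverse events, the protocol article gives the task to one role: "The physical therapist will record any adverse event occurring in this study". No other recorder is named in the article.

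The two arms meet that role very differently:

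- **Experimental arm** (Experimental intervention program): patients receive "one or two sessions weekly in the hospital under the supervision of a physiotherapist and one session per day at home under parental supervision", for 6 months.
- **Control arm** (Control group program): "The control group will only attend study assessments and not the therapy sessions". The Discussion puts this at two occasions: "The control group only needs to perform the assessment at the baseline and after the 6-month intervention".
- **Who does the assessments** (Randomization and masking): "A trained evaluator blinded to group allocation will complete all patient assessments at baseline and immediately after the 6-month intervention". Assessment and treatment take place in separate rooms.
- **Blinding of the recorder** (same section): "physical therapists and patients cannot be blinded when offering or receiving the treatment".

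The Interim analysis section gives the therapist one further task that spans both arms: "The reasons for withdrawal from trial by arm will be calculated by the physical therapist".

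Harms adds only a rule for passing events to the ethics committee when a causal link with the intervention is suspected, and states that no risk is expected in either group. Compliance supervision describes a messaging app, run by the research assistant, that includes all patients. Its listed uses are training checks, questions, health information and visit reminders.

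**The concern.** An adverse event count reflects both how often events happen and how often someone is there to hear of them. Here the named recorder is scheduled to be present weekly in one arm and not at all in the other. If true risks were equal, the recorded counts would still tend to be higher in the exercise arm. A reader of a by-arm table could not separate a harm of exercise from the effect of closer observation.

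Three uses of the data depend on this. The protocol's expectation of no risk for patients without the intervention could not be checked well. The monitoring board, which reviews all data, would see counts from unequally observed arms. The tally of withdrawal reasons by arm, which helps in judging missing data on the primary outcome, is assigned to the same person.

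**Working it through.** The article states no adverse event rate and no figure for this point, so there is nothing of the plan's own to reproduce. The check has three steps.

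**1. Scheduled contacts with the recorder.** Inputs are one or two supervised sessions a week (Experimental intervention program) and 6 months taken as 26 weeks.

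- Experimental: 26 × 1 = 26 to 26 × 2 = 52 per patient (24 to 48 if 6 months is taken as 24 weeks).
- Control: 0 with the therapist, and 2 visits with the blinded evaluator.

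**2. Is there another stated route for control-arm events?**

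- Evaluator visits: the listed measures are Cobb angle, trunk rotation, sagittal index and SRS-22. No adverse event query is among them. The SRS-22 pain domain is a score, not an event record.
- Messaging app: it reaches both arms but is not described as an adverse event route.
- Harms section: it governs onward reporting, not collection.
- Withdrawal tally: it implies that some control-arm information reaches the therapist, but not how, and not for events short of withdrawal.

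So no symmetric route is described, though some control-arm capture is possible.

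**3. How large could the distortion be?** Let the true risk be p in both arms, and let the capture probabilities be s_E and s_C. Then

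- expected patients with a recorded event in an arm = 21 × p × s
- spurious risk difference = p × (s_E − s_C)

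The 21 per arm is from Sample measurement. The values of p, s_E and s_C are assumptions. With p = 0.20 and s_E = 0.90, the experimental arm records 21 × 0.20 × 0.90 = 3.78.

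| Control capture s_C | Recorded, experimental | Recorded, control | Spurious difference |
|---|---|---|---|
| 0.90 | 3.78 | 3.78 | 0.20 × 0.00 = 0 |
| 0.50 | 3.78 | 2.10 | 0.20 × 0.40 = 8 points |
| 0.25 | 3.78 | 1.05 | 0.20 × 0.65 = 13 points |
| 0 | 3.78 | 0 | 0.20 × 0.90 = 18 points |

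The upper end moves with the true risk: 0.10 × 0.90 = 9 points at 10%, and 0.30 × 0.90 = 27 points at 30%. The lower end is 0 whenever capture is equal.

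**The case against.** The strongest reply is that one sentence in a condensed article cannot be expected to carry forms and query schedules, and that the sentence covers any event in the study, hence both arms. It does not say that nobody else may report an event to the therapist. Barring controls from therapy sessions does not bar all contact, and the withdrawal tally suggests that some control information arrives. All of this stands. It means that a reader who inferred that the therapist is the exclusive recorder, or never sees a control patient, or that the data are biased by construction, would be going beyond the text.

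Four further inferences also fail:

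- **A biased planned analysis.** The analysis section lists Cobb angle, trunk rotation, sagittal index and quality of life. No between-arm test of harms is planned.
- **A spurious significant result.** With 21 per arm, Fisher's exact test gives p = 0.048 for 5 against 0 events. That presumes full capture in one arm and none in the other. With the same 5 events, 1 recorded control event gives p = 0.18 and 2 give p = 0.41. The zero-capture figure is a limiting case, not an estimate.
- **Harms of non-treatment go unseen.** Curve progression is the primary outcome and pain is an SRS-22 domain; both are measured in both arms.
- **Control events fail to reach the ethics committee.** The Harms section sends on only events suspected to be caused by the intervention, so most control events would not go there, whoever recorded them.

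What the reply does not remove is the assignment itself. The article does more than leave out detail: it names a recorder whose scheduled contact is with one arm only.

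**Conclusion.** The point holds in a limited form. The sole named recorder is unblinded and has about 26 to 52 scheduled contacts per experimental patient and none per control, and no collection route common to both arms is described. Any adverse event counts displayed by arm, and by extension the by-arm withdrawal reasons, are open to differential ascertainment, most likely as under-recording in controls.

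The size is unknown. The range of 0 to 18 percentage points rests wholly on an assumed 20% true risk in both arms, 90% experimental capture and control capture between 90% and 0%. It shows what is possible, not what to expect. Measurement of the planned primary and secondary outcomes is untouched, so the matter is of moderate weight. It still deserves correction during the trial, because unasked events are hard to recover once follow-up has ended.

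**What to change.** Ask the same adverse event question in both arms on the same schedule:

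- a short self-completed patient or parent form at the 6-month visit, returned to someone other than the blinded evaluator so that answers do not reveal allocation;
- the same question at fixed intervals through the messaging app already in use for all patients.

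Base any by-arm display on this source. Keep the therapist's notes, but list them separately as events found through treatment contact. Take withdrawal reasons from the same common source, so that the therapist's tally does not depend on who happened to be in contact.

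The cost is a one-page form, a repeated message and a little more data entry, using contacts that already exist. Patients will still know their arm, so some difference in self-reporting may remain. The change equalises the opportunity to report, which is the part the plan controls.
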